#### 3. Digital therapy offers

During the entire care process and after the onboarding performed by the personal pilots, digital intervention in terms of physical training courses and psychological interventions are provided to the patients. Patients can take part individually, regardless of location and time (so-called asynchronous offers [30]). The digital therapy services will support the treatment and bridge any waiting times for the patients in the IG to get the assessment and other therapies, as well as to support any indicated rehabilitation measures (cf. [33]). Patients in the IG will receive digital interventions on the basis of their physical resilience and patients in the ACG will receive one of three digital interventions based on their leading symptoms (fatigue, cardio-/respiratory, neuro-psychiatric).

In addition to the content of the digital tool, an interactive chatbot will be developed and tested during the duration of the ASAP project. The chatbot will focus more on short interventions targeting the management of symptoms in daily life, including self-discrepancies, pacing, and coping.

The patients will receive information and training to initiate the treatment of the present symptoms and to strengthen their self-management as well as to contribute to psychological stabilization. Contents include training in relaxation/breathing exercises, autogenic training, mindfulness/relaxation exercises, meditation, muscle relaxation as well as psychoeducation, strength training, physical endurance and coordination training, sensory training (including smell and taste), functional training as well as training on how to deal with the disease in an occupational context (cf. [34]).

Using this method and determining differences in the IG (patients who receive individualized digital offers on basis of their physical resilience), ACG (patients who received individualized  offers based on the most debilitating symptoms) and CompG (patients who only received the chatbot on a voluntary basis) in the questions about how effective they found the digital interventions in the treatment of PACS allows us to test Hypothesis 3. Within this hypothesis, it is assumed that the more individualizable digital interventions are, the better they work. To assess this, we will check whether IG, ACG and CompG differ in terms of the development of symptoms, increased activities of daily lives, RTW and increase social participation with individualization as another factor. To do so, we will consider MANOVA and repeated measurement ANOVA analyses considering individualization accordingly.

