### The Research Project

The objective of the present study is the early detection of post-acute COVID-19 symptoms (PACS) and subsequently a long-term and sustainable holistic care and support of patients with PACS to avoid long-term illness and chronification, and to enable social participation.

The long-term goals of the study are the dissemination of validated instruments (i.e.g., the online screening) and newly developed treatment approaches (i.e., the digital interventions and a  personal pilot concept) through communication to central stakeholders such as medical associations, health insurance companies, service providers in the outpatient and inpatient sector as well as professional societies and care institutions. In this way, patient care is to be improved beyond the project duration and care services are to be made more efficient.

Hypotheses, which will be tested with this project, are the following:A short *screening* can detect the presence of PACS.A comprehensive* assessment* can validly and reliably determine rehabilitation or remedial needs and the leading rehabilitation indication and be basis of an individual multidisciplinary treatment plan.The more *individualization* the digital therapy offers, the higher the effectiveness in the treatment of PACS.As contact point for all involved parties, a *personal pilot * empowering the patient suffering from PACS can -by means of an interdisciplinary and intersectoral treatment planning- ensure the sustainable management of interdisciplinary treatment.An *interdisciplinary treatment pathway* and the personal pilots empower the patients, so that the patients receive the appropriate diagnosis and treatment, and to actively participate in their own recovery, ensuring patients recover quickly and sustainably from their PACS conditions, increase their functional capacity, reduce incapacity to work and regain participation.

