Internal diagnostics	• Echography • Carotis-duplex sonography

The results of the assessment for each professional group will be handed to a clinician, who is then able to make a holistic assessment of whether PACS is present or not. These assessments are also summarized to form a holistic treatment plan, which synopsizes the findings and lists the indicated medical and therapeutic measures. These recommendations will be made visible for the personal pilot, and subsequently made available to the attending outpatient doctor.

The prescription of necessary treatments and aids, as well as the recommendation of digital interventions already take place within the framework of discharge management. If the need for a rehabilitation measure is determined, this will be communicated to the patient directly in a way to enable him/her applying for rehabilitation treatment and finding the most appropriate treatment within Germany (also with the help of the personal pilot).

Using such an approach allows us to test Hypothesis 2, that a comprehensive assessment can determine rehabilitation or remedial needs and the leading rehabilitation indication. To assess the applicability of this hypothesis, we will consider a comparison of test–retest reliabilities of the degree of experienced symptoms in the IG compared with the ACG and the CompG. Furthermore, the assessment allows us also to test Hypothesis 5 that an interdisciplinary treatment pathway empowers the patient. To assess the applicability of this hypothesis we will check whether IG, ACG and CompG differ in terms of the development of symptoms, increased activities of daily lives, RTW and increased social participation. To do so, we will consider MANOVA and repeated measurement ANOVA analyses.

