#### Type of statistical analysis used

To test the aforementioned hypotheses, first, a propensity score matching will be applied between the IG and the CompG. Sensitivity analyses and test–retest reliabilities will be used to test Hypothesis 1 and 2 respectively. To test Hypothesis 3, MANOVA and repeated measurement ANOVAs will be used. To assess Hypothesis 4, no statistical analyses but a qualitative approach will be used. For the last hypothesis (Hypothesis 5), repeated measurement ANOVAs and MANOVAs will be used.

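### Hypothesis 3 (more individualization, more effect) is tested by whether three groups differ, so a lag of the non-randomised CompG alone can produce a significant result

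*Protocol article*

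**What the plan says.** The hypothesis list under The Research Project states Hypothesis 3 as an ordered claim: the more individualization in "the digital therapy offers, the higher the effectiveness in the treatment of PACS". The section 3. Digital therapy offers restates it beside its test: "it is assumed that the more individualizable digital interventions are, the better they work".

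The test follows: "To assess this, we will check whether IG, ACG and CompG differ in terms of the development of symptoms", and likewise in activities of daily living, return to work and social participation, "with individualization as another factor". Type of statistical analysis used repeats only the method: "To test Hypothesis 3, MANOVA and repeated measurement ANOVAs will be used". Sample size planning sets a two-sided p-value below 0.05. For Hypothesis 5, section 2. Comprehensive assessment program puts the same group question: "To assess the applicability of this hypothesis we will check whether IG, ACG and CompG differ in terms of the development of symptoms". The two tests differ only in the individualization factor.

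The groups are described as follows.
- **IG:** digital offer tailored to physical resilience in three categories, after a 3-day assessment, with a personal pilot.
- **ACG:** digital offer tailored to the leading symptom, also in three categories, with a personal pilot and no assessment.
- **CompG:** recruited separately and not randomised, without a pilot. It is described as untreated in Study design and setting, and as having only a voluntary chatbot in section 3. Propensity matching is planned between IG and CompG only.

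**The concern.** A three-group test takes equality of all three groups as its null, and any inequality as its alternative. Hypothesis 3 is narrower: it claims an order along a gradient of individualization. A significant result can therefore arise without the two randomised arms differing at all, provided the CompG does worse.

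The CompG differs from the other two groups in several ways besides individualization: recruitment route, lack of randomisation, lack of a pilot, and little or no digital training. If the p-value from the stated test is taken as the answer to Hypothesis 3, individualization may be credited with a difference that the pilots, any digital content at all, or self-selection produced. The outcomes tested include both primary endpoints, symptom reduction and return to work.

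**Working it through.** **1. The plan's own figure.** Sample size planning gives 68% power for N = 132 (66 IG, 66 ACG), alpha 0.05 and an effect of 0.15, for a within-between interaction. With the noncentral F formula λ = f²·N·m/(1 − ρ), reading 0.15 as f and assuming m = 2 measurements and ρ = 0:

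λ = 0.15² × 132 × 2 = 5.94; df = 1 and 130; critical F = 3.914; power = 0.677.

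This reproduces the 68% with two groups. The only comparison that was sized is thus IG v ACG; the CompG is not in the calculation. The text does not tie this calculation to Hypothesis 3.

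**2. Does the individualization factor change the test?** The article gives it no levels, order or within-arm measure. Individualization is described only by what each arm receives: resilience-based (IG), symptom-based (ACG), voluntary chatbot (CompG). A factor with one value per arm is aliased with group, so it adds no information beyond the group term. A factor in ANOVA is also unordered, and its F test has no direction.

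**3. How often the three-group test rejects when IG = ACG.** One-way F test on a change score with SD 1:

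λ = Σ nᵢ(μᵢ − μ̄)², with df = 2 and N − 3, where μ̄ is the size-weighted mean.

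Assumed means (better is higher): IG 0.5, ACG 0.5, CompG 0. Assumed sizes: the planned 66/66 with a CompG of 66; and the 1:2 dice ratio applied to 132 (44/88) with a CompG of 44, matched 1:1 to the IG.

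- 66/66/66: μ̄ = 0.333; λ = 132 × 0.167² + 66 × 0.333² = 11.0; df 2, 195; critical F = 3.042; rejection 85%.
- 44/88/44: μ̄ = 0.375; λ = 132 × 0.125² + 44 × 0.375² = 8.25; df 2, 173; critical F = 3.048; rejection 72%.

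With a smaller CompG lag of 0.3 SD, λ is 3.96 and 2.97, and rejection is 41% and 31%.

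**4. What the randomised contrast shows in the same setting.** In a simulation of 20,000 runs at 66/66/66 with a 0.5 SD lag, the three-group test rejected in 85% of runs. IG was significantly better than ACG in 2.4%, which is the chance rate for one tail of a two-sided 0.05 test.

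**5. Order.** At 66/66/66, means of (0.5, 0.25, 0) and (0.25, 0.5, 0) for IG, ACG and CompG give the same λ, 66 × (0.25² + 0.25²) = 8.25, and so the same rejection rate, 72%. The p-value does not distinguish the two orders; the means do.

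**The case against.** The strongest reply is that the article never says an omnibus p-value decides Hypothesis 3. It names a question and a family of methods, and follow-up contrasts may stand in a full protocol or analysis plan that is not shown. This stands in part: the absence of named contrasts is not in itself a finding. What remains is that the article fixes both the question and the method, and that question does not match the hypothesis printed beside it.

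Second, individualization is named as a factor. If it were a graded measure taken within arms, that term could carry the test. No such measure is described, so as written it does not help, but defining one would be a legitimate answer.

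Third, IG = ACG with a worse CompG is partly compatible with Hypothesis 3, because the article calls both the IG and the ACG offers individualized. This stands. Such a pattern does not contradict the hypothesis; it cannot be attributed to individualization, because the CompG also differs in pilot, recruitment and randomisation.

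A reader might infer more: that the plan would count a better ACG as support for a better IG. The documents do not support that. Any two-sided test rejects in both directions, and the group means would reveal a reversed order. A reader might also infer that the randomised comparison has been sidelined, but the sample size rests on exactly that comparison.

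Finally, IG v ACG is not a pure test of digital individualization either, because the IG also receives the 3-day assessment and the resulting treatment plan. This stands and belongs in the fix.

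**Conclusion.** The concern holds in a limited form. The stated test of Hypothesis 3 can be significant because of the CompG alone, with the randomised arms equal, and such a result cannot be attributed to individualization. The individualization factor as described does not prevent this.

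The rates are 85% (66/66/66) and 72% (44/88/44) for a CompG lag of 0.5 SD, and 41% and 31% for 0.3 SD. They rest on assumed effects, an assumed CompG size and a single change score; the article gives none of these. They illustrate how the test behaves and do not forecast the trial's result.

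This should be fixed, but it is not critical. Hypothesis 3 is one of five, the randomised comparison is available, and the remedy is wording. The case of a better ACG is secondary.

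**What to change.** - State how the arms rank on individualization. The Abstract calls the ACG programme more common, while later sections call both offers individualized.
- Make the test of Hypothesis 3 the IG-minus-ACG contrast in change from T1 to one named time point (for example T4, after the digital interventions), in randomised patients only, two-sided at 0.05. This leaves out patients placed in the ACG without randomisation. Count the hypothesis as supported only if the contrast favours the arm ranked as more individualized. Since four outcomes are listed, name the one that decides.
- Report contrasts with the CompG separately, as non-randomised context and not as the deciding test.
- State that IG v ACG also includes the 3-day assessment, so that a difference supports the individualized package and not digital individualization alone.

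The cost is a change of wording, with no new data. The downside is that Hypothesis 3 will be supported less often, because a difference from the CompG no longer counts.

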**Methods:**

This German study consists of a low-threshold online screening for PACS where positively screened participants will be supported throughout by personal pilots. The personal pilots are aimed at empowering patients and helping them to navigate through the study and different treatment options. Patients will then be randomly assigned either to an intervention group (IG) or an active control group (ACG). The IG will receive a comprehensive assessment of physiological and psychological functioning to inform future treatment. The ACG does not receive the assessment but both groups will receive a treatment consisting of an individual digital treatment program (digital intervention platform and an intervention via a chatbot). This digital intervention is based on the needs identified during the assessment for participants in the IG. Compared to that, the ACG will receive a more common digital treatment program aiming to reduce PACS symptoms. Importantly, a third comparison group (CompG) will be recruited that does not receive any treatment. A propensity score matching will take place, ensuring comparability between the participants. Primary endpoints of the study are symptom reduction and return to work. Secondary outcomes comprise, for example, social participation and activities in daily life. Furthermore, the feasibility and applicability of the online screening tool, the holistic assessment, digital trainings, and personal pilots will be evaluated.

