**Fig. 3 Fig3:**
[figure not shown]
Flowchart of the study design. *IG* Intervention Group, *ACG* Active Control Group

Patients are invited via primary care physicians, support groups, press releases, and social media. Participants may take part when they show signs of PACS symptoms that last longer than 4 weeks after the acute COVID-19 infection. All participants will first take part in a low-threshold *online screening*. Following the online screening, patients receive direct feedback as to whether they are suitable to take part in the study (i.e., whether there are indicators of risk factors of the presence of PACS). Shortly after the positive screening patients from the IG and ACG receive their first contact with a personal pilot.

Patients from the IG and the ACG will then receive unspecific *digital interventions* (e.g., hygiene recommendations etc.). In the IG, this unspecific digital intervention will be made available to bridge the time to an assessment that takes place in a clinic and in which patients will be assessed by a multiprofessional team of health care professionals. After the assessment, patients in the IG receive digital interventions that aim to meet their individual needs in terms of their physical capacity (i.e., physically very resilient, moderately resilient, barely resilient); patients in the ACG receive digital interventions that are individualized based on the most debilitating symptoms (fatigue, neuro-cognitive symptoms, cardio-respiratory). The digital intervention tools consist of training plans on the one hand and additionally, a chatbot will be developed and made available to complement the interventions on the other hand. This chatbot will answer specific questions of participants, for example, about symptoms or who to contact first, and it will also contain short psychological “learn”, “think”, “do”, exercises to improve participants well-being.

In the IG, a 3-day multidisciplinary *assessment* will be carried out promptly at a clinic to determine the individual need for treatment, the results of which are used as the basis for holistic treatment planning. Possible treatment recommendations are the initiation of rehabilitation, the provision of medical aids, specific therapies, the recommendation of digital health applications, and outpatient treatments.

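### Individualization is fixed by arm as described, so the extra factor for Hypothesis 3 adds nothing to the group comparison and cannot separate tailoring from the rest of the package

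*Protocol article*

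**What the plan says.** Hypothesis 3 (The Research Project) is a more-is-better claim. The section 3. Digital therapy offers restates it: "Within this hypothesis, it is assumed that the more individualizable digital interventions are, the better they work". The same section describes the arms:

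- IG: "IG (patients who receive individualized digital offers on basis of their physical resilience"
- ACG: "patients in the ACG will receive one of three digital interventions based on their leading symptoms"
- CompG: "CompG (patients who only received the chatbot on a voluntary basis"

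It says that differences between these groups on questions about perceived effectiveness allow Hypothesis 3 to be tested. It then adds a comparison of the three groups on symptoms, daily activities, return to work and social participation, with individualization as a further factor, by "MANOVA and repeated measurement ANOVA analyses considering individualization accordingly".

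For Hypothesis 5 (interdisciplinary pathway and personal pilots), the section 2. Comprehensive assessment program says "we will check whether IG, ACG and CompG differ in terms of the development of symptoms" and goes on to list the same other three outcomes and the same two types of model. Type of statistical analysis used repeats that pairing.

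Under Evaluation concept, one die roll allocates patients to IG or ACG. CompG is recruited through a separate link, and propensity matching is planned between IG and CompG.

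**The concern.** A factor has an effect of its own only if it varies among patients who share the same levels of the other factors. Here the mode of individualization appears to be settled once the arm is known. If so, the model has nothing left to attribute to individualization after group. Dropping group in favour of individualization would merely rename the group test.

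The project intends to disseminate its digital interventions and its pilot concept as products in their own right (The Research Project; Dissemination of the study results). A group difference read as evidence for one component would go beyond what the design can show.

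**Working it through.** **Inputs.** Arm descriptions from 3. Digital therapy offers and Study design and setting; allocation from Evaluation concept; the IG-only assessment from the Abstract (Methods) and 2. Comprehensive assessment program; pilots from Study design and setting and 4. Personal pilot. The plan gives no figure for this point to reproduce. Its sample-size statement (N = 132, 68% power, d = 0.15) plays no part.

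**Step 1: is the factor separate from arm?** Let g be the individualization code. If each arm has one code, then for every patient

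g = g(IG)·1[IG] + g(ACG)·1[ACG] + g(CompG)·1[CompG],

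which is a linear combination of the arm indicators. The added column lies in the space that arm already spans. Numerical check of the design rank:

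| Design | Rank, arm only | Rank, arm + individualization |
|---|---|---|
| Three arms, categorical factor (5 columns) | 3 | 3 |
| Three arms, linear score | 3 | 3 |
| Three arms, with interaction | 3 | 3 |
| IG and ACG only | 2 | 2 |
| Three arms × 2 time points | 6 | 6 |
| Three arms × 6 time points | 18 | 18 |

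Added degrees of freedom: 3 − 3 = 0, and likewise 0 in every other row. The added sum of squares is 0.

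**Step 2: what if individualization replaces arm?** In two simulated data sets (arms of 66/66/66 and 44/88/66), the F statistic for individualization alone equalled that for arm alone: 2.229 in both models for the first, 1.458 in both for the second. It is the same test.

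**Step 3: what do the group differences contain?** Assume, for illustration, that components add. Let A be the assessment with its plan and recommendations, Dr the resilience-based programme, Ds the symptom-based programme, C the voluntary chatbot in CompG, P the pilot, and S the selection difference between CompG and the randomised patients. Then

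- IG − ACG = A + (Dr − Ds)
- ACG − CompG = (Ds − C) + P + S
- IG − CompG is the sum of these two.

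There are two independent differences and five unknown terms: A, Dr − Ds, Ds − C, P and S. The Hypothesis 3 quantity Dr − Ds always appears together with A. P cancels from the randomised contrast, because both randomised arms have pilots, and appears only together with S. Matching on measured characteristics may reduce S between IG and CompG, but it does not turn that comparison into a randomised one.

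**Step 4: overlap with Hypothesis 5.**

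| | Hypothesis 3 | Hypothesis 5 |
|---|---|---|
| Groups | IG, ACG, CompG | IG, ACG, CompG |
| Symptoms, daily activities, return to work, participation | yes | yes |
| Perceived effectiveness of digital interventions | yes | no |
| Models | MANOVA, repeated-measures ANOVA | MANOVA, repeated-measures ANOVA |
| Further factor | individualization (0 df if set by arm) | none |

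On the four shared outcomes the two tests coincide. On the perceived-effectiveness questions Hypothesis 3 has its own outcome, but the contrast is still between arms and still carries A, P and S.

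**The case against.** The strongest reply is that the protocol never says the factor is coded by arm. Treatment does vary within arms: three resilience classes in IG, three symptom programmes in ACG, voluntary chatbot use in CompG, and a move from unspecific to tailored content over time in both randomised arms. An analysis plan that is not shown might define a patient-level measure, and the rank result depends on the one-code-per-arm reading. That dependence is real. But the resilience classes and symptom programmes are kinds of content, not degrees of individualization, and the early unspecific phase changes with time rather than between patients within an arm. The article itself says that comparing these three groups allows Hypothesis 3 to be tested. A patient-level measure, if one existed, would give an observational comparison and not a randomised one.

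Four stronger inferences are tempting, and the documents do not support them:

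- **Hypotheses 3 and 5 are one test throughout.** The perceived-effectiveness questions belong only to Hypothesis 3.
- **The documents contradict each other on whether IG is more individualized.** Study design and setting says "patients in the ACG receive digital interventions that are individualized based on the most debilitating symptoms", and the Abstract says "the ACG will receive a more common digital treatment program". But the Abstract also calls both programmes individual and bases IG's on needs found at assessment, which implies an ordering of IG over ACG. The wording is loose, not contradictory.
- **Only IG receives referrals.** The section 4. Personal pilot says that pilots support referral in both randomised arms. What is specific to IG is the assessment and the plan and recommendations drawn from it.
- **The plan announces that one difference will prove two mechanisms.** It does not; its language is about checking applicability. Hypothesis 4, the dedicated pilot hypothesis, is handled qualitatively, and the methods text restates Hypothesis 5 mainly as a pathway claim. Its formulation under The Research Project still names the pilots.

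**Conclusion.** The point stands in this form. With individualization set by arm, the further factor contributes 0 degrees of freedom, and Hypothesis 3 cannot be separated from the arm effect. On the four shared outcomes it is tested by the same comparison as Hypothesis 5. IG v ACG remains a valid randomised comparison of packages among patients who were actually randomised; patients who could not be randomised are placed in ACG and marked. The pilot part of Hypothesis 5 has no randomised contrast.

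The conclusion rests on the arm descriptions in the article and on the absence there of any patient-level degree of individualization. It does not depend on how the arms are ranked or on the additive model used for illustration. A reader might want to say that anything from none to all of an IG–ACG difference could be due to digital tailoring. That expresses non-identifiability and is not a computed range; if components worked in opposite directions, the share could lie outside it.

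**What to change.** 1. In 3. Digital therapy offers, delete individualization as a further factor in the MANOVA and repeated-measures ANOVA.
2. State that IG v ACG estimates the effect of the whole package: assessment, treatment plan and resilience-based programme against the symptom-based programme.
3. Confine Hypothesis 5 to that package.
4. Label Hypothesis 3, including its perceived-effectiveness questions, and any personal-pilot effect as exploratory, with no confirmatory claim.

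The cost is wording and fewer confirmatory claims. No new data, arms or measurements are needed, and the randomised package comparison is untouched.
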